### Sample size

2.4

Since the main efficacy index of this study is the total effective rate, the sample size will be estimated according to the total effective rate of pre-experiment. According to the preliminary clinical pre-experiment, the total effective rate of TC combined with sodium hyaluronate was 91.3%, and that of sodium hyaluronate was 68.57%. PASS15.0 will be used for sample size estimation, and an optimal design will be adopted. α = 0.05, β = 0.2, test efficiency = 0.8, the number of experimental group: the number of control group = 1:1, threshold = –0.4. According to the software calculation, the total sample size of the 2 groups will be 130 cases, and 146 cases will be finally included considering the clinical shedding rate of about 10%. The included patients will be numbered according to the order of treatment and divided into the treatment group and the control group by completely random method, with 73 cases in each group.

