#### Efficacy indicator

2.6.2

Main efficacy indicators: total effective rate: according to *Guiding Principles for Clinical Research of New Chinese Medicine*,^[21]^ total effective rate = (clinical control + significantly effective number + effective number)/total number of people × 100%. ① Clinical control: pain and other symptoms disappear, joint activity is normal, integral reduction ≥95%; ② Significantly effective: pain and other symptoms disappear, joint activity is not limited, 70% ≤ integral reduction < 95%; ③ Effective: pain and other symptoms basically disappear, joint activity is slightly limited, 30% ≤  integral reduction < 70%; ④ Ineffective: no significant improvement in symptoms such as pain and joint activity, integral reduction < 30%.

Secondary efficacy indicators: changes in osteoarthritis index score, knee joint score, and balance index

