### Sample collection

2.7

Data will be collected according to the evaluation criteria before and 5 weeks after the treatment, and telephone follow-up will be conducted for 3 months after the treatment. If follow-up information cannot be collected, the reasons for loss of follow-up shall be recorded in detail. Access to the database is restricted to the researchers in this research group.

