### Statistical analysis plan

2.9

Use Excel to build database. Full analysis set: including all subjects randomly enrolled, treated and visited at least once, and use full analysis set for intent-to-treat analysis. Per-protocol set: including all subjects who comply with the trial protocol, have no missing baseline variables, and have measurable major variables. Safety set: including subjects randomly enrolled, treated at least once and being safe after at least 1 treatment.

SPSS25.0 statistical analysis software will be used for data analysis in this study. If measurement data meet normal distribution, independent-sample *t* test will be used between groups and paired-sample *t* test will be used within groups; if not, non-parametric test will be used and the results will be expressed in quartiles; Chi-square test will be used for counting data. The incidence of adverse events is compared by chi-square test. When *P* *<* *.05*, the difference is statistically significant.

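### The primary responder comparison is an unadjusted chi-square test; adjusting for the baseline score already collected would be a cheap improvement, with a gain the documents do not let us fix

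*Protocol article*

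**What the plan says.** Section 2.6.2 (Efficacy indicator) sets the primary: "Main efficacy indicators: total effective rate". A patient counts as effective or ineffective. The grades combine wording on symptoms and joint activity with a percentage reduction of an unnamed *integral*, and the lowest effective grade needs a reduction of at least 30%.

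Section 2.9 (Statistical analysis plan) assigns tests by type of data, and for a binary endpoint the rule is "Chi-square test will be used for counting data". It names no covariate and no stratified analysis.

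Section 2.4 (Sample size) says patients will be "divided into the treatment group and the control group by completely random method", with no stratification factor. It gives the planning rates: "the total effective rate of TC combined with sodium hyaluronate was 91.3%, and that of sodium hyaluronate was 68.57"%.

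Section 2.7 (Sample collection) says "Data will be collected according to the evaluation criteria before and 5 weeks after the treatment", so pre-treatment scores will be on file.

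**The concern.** The percentage reduction cannot be calculated without each patient's own baseline value, so the value has to be collected. As written, it then plays no part in the allocation or in the test that decides the trial. If patients who start worse are less (or more) likely to be graded effective, part of the variation in response could be explained by baseline, and an unadjusted test leaves it in the error term. A severity difference that arises by chance in one realised trial also stays in the estimated effect. Adjusting the secondary scores would not reach this, because the primary is a separate binary comparison.

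What is at stake is efficiency. It matters most if the true difference is smaller than the 22.73 points seen in the pre-experiment.

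**Working it through.** **Inputs from section 2.4.** Rates 0.913 and 0.6857 (difference 0.2273); "α = 0.05, β = 0.2, test efficiency = 0.8"; 1:1 allocation; 130 patients before and 146 after dropout. Two-sided testing is assumed. The association between baseline and response is not given, so it is varied below.

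**1. The plan's own size.** The usual pooled formula at 80% power gives

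n = [1.96·√(2 × 0.79935 × 0.20065) + 0.8416·√(0.913 × 0.087 + 0.6857 × 0.3143)]² / 0.2273² = 47.5, so 48 per arm and 96 in total.

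The stated 130 is not reproduced, and the role of "threshold = –0.4" is not explained. That is a separate matter. The dropout step does reproduce: 65/0.9 = 72.2, rounded up to 73 per arm, or 146. For this point, the consequence is that 65 per arm gives more power than the 80% stated.

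**2. Unadjusted power** (normal approximation, unpooled standard error).
- Planned rates, 65 per arm: SE = √(0.294946/65) = 0.0674; 0.2273/0.0674 = 3.374; power = Φ(3.374 − 1.96) = 0.92. The pooled form gives 0.91.
- 60% of the planned difference (0.6 × 22.73 = 13.64 points, so 82.2% against 68.57%), 73 per arm: SE = 0.0704; ratio 1.937; power = Φ(1.937 − 1.96) = 0.49. The pooled form gives 0.48.

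**3. Variance ratio R (adjusted over unadjusted)** for a risk difference standardised from a logistic model with baseline.

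| Assumption on baseline and response | R |
|---|---|
| No association | 1.00–1.01 |
| Log-odds per baseline SD 0.5 / 1.0 / 1.5 (simulated, 65 per arm) | 0.97 / 0.89 / 0.81 |
| Latent correlation 0.3 / 0.5 / 0.6 (simulated) | 0.96 / 0.82–0.88 / 0.79–0.81 |
| Response is only a 30% reduction; baseline–follow-up correlation 0.3 / 0.5 / 0.7, equal SDs (asymptotic) | 0.93 / 0.98 / 1.00 |

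The last row shows that dividing by baseline can remove the association: at correlation 0.7 nothing is gained.

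**4. Adjusted power** = Φ(ratio/√R − 1.96).
- Planned rates, 65 per arm: R = 0.98 gives 0.926; R = 0.93 gives 0.938; R = 0.81 gives 0.963. Simulation at log-odds 0.5 / 1.0 / 1.5 gave 0.93 / 0.95 / 0.97 against about 0.92 for chi-square.
- 60% of the difference, 73 per arm: R = 0.98 gives 0.50; R = 0.93 gives 0.52; R = 0.80 gives 0.58.
- No association (R = 1.01): 0.919 instead of 0.921, and 0.487 instead of 0.491.

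**5. Type I error.** In simulation with no treatment effect, chi-square rejected in 4.9 to 5.3% of trials. The standardised risk difference rejected in 5.2 to 5.9% with a simple standard error, and in about 5% with a small-sample one.

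**6. Chance imbalance.** A baseline difference of 0.2 SD moves the unadjusted risk difference by 0 to 2 points when response is only the 30% cut. For log-odds of 0.5 to 1.5 per SD it moves it by 1.5 to 3.2 points (slopes 0.075 to 0.161 per SD, times 0.2).

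**The case against.** The strongest reply is that nothing here is wrong. A chi-square test on a randomised binary outcome holds its error rate, matches a sample size built on two crude proportions, and already allows for chance imbalance. That stands. A reader might infer that the primary result is biased or its test invalid because baseline is left out; the documents do not support this, since randomisation balances baseline in expectation.

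A second reply is that the gain rests on an association nobody has documented. This also stands. A reader might infer that baseline must be prognostic because it enters the percentage reduction, but the last row of the table shows otherwise. It does not follow that the gain is nil. The grades also describe end states, such as symptoms having largely gone, and these may be harder to reach from a worse start. With invented end-state cut-offs (final score at most 30 or 20 on a 0–100 scale, baseline mean 50) added to the 30% cut, R ran from 1.00 at correlation 0.3 down to 0.75 at correlation 0.7. Those cut-offs are not in the protocol, so the range shows only that the answer could go either way.

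Third, the covariate is unidentified, because the integral is not named, and section 2.9 implies that some baseline values may be missing, since it makes complete baseline data a per-protocol condition. Both stand, and the fix must deal with them. The worry that a model would inflate the error rate, with only about 6 non-responders expected in the experimental arm (0.087 × 65 = 5.7), is met by a small-sample standard error.

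Last, a condensed article may leave adjusted analyses to a fuller plan. But this article states the test, and the point concerns that stated choice. If a fuller plan already prespecifies an adjusted primary analysis, the point falls away.

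**Conclusion.** The point holds as a low-cost improvement to a stated and valid method. The primary test ignores a baseline value that the trial collects and that allocation does not balance by stratification. If that value predicts response, precision is lost: about 0 to 7% of variance if response is only the 30% cut, and up to about 20% if baseline is strongly prognostic. At the planned rates with 65 per arm the effect is small, from about 92% power to about 93 to 97%. It is more useful if the pre-experiment was optimistic: at 60% of the planned difference with 73 per arm, power goes from about 48% to about 50 to 58%.

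These figures assume two-sided testing at 0.05, the planning rates in section 2.4 (or 60% of their difference), and a strength of association that the documents do not supply. A firm statement that the plan loses precision would go beyond them; *may lose* is as far as they reach.

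**What to change.** In section 2.9, before any outcome data are seen:

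- Name the score behind the integral in section 2.6.2.
- Make the primary analysis a logistic regression of effective versus ineffective on group and the baseline value of that score.
- Report it as a standardised risk difference with a 95% confidence interval and a small-sample standard error.
- State how a missing baseline value will be handled.
- Keep the chi-square test as a supportive analysis.

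The cost is a few sentences and a primary result that comes from a model rather than a two-by-two table. The standardisation and its standard error go a step beyond routine logistic output. If baseline turns out not to be prognostic, there is essentially no gain and about a 1% variance cost. The quantity estimated, a difference in effective rates, stays the same, and the sample size need not change.

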## Discussion

3

Clinically, non-steroidal anti-inflammatory drugs, glucocorticoids, intra-articular injection of sodium hyaluronate, and other related drugs are usually used for the treatment of KOA patients, which can relieve pain in a short term,^[22]^ but the efficacy of these drugs is not stable. In addition, it has different degrees of gastrointestinal reactions, liver and kidney damage, toxic and side effects on chondrocytes, and other adverse reaction.^[23,24]^ Sodium hyaluronate is a physiologically active substance widely found in human body with high viscosity. Under the condition of abnormal stress of articular cartilage, it can reduce vibration and play a role in lubrication and joint protection.^[25]^ Injection of sodium hyaluronate can significantly improve the inflammatory response of synovial fluid tissue and delay the progression of KOA.^[26]^ Clinical studies have confirmed that joint dysfunction and reduced balance ability can be improved through exercise training.^[27]^

TC is regarded as a kind of exercise that alternates muscle contraction training with total body relaxation. Studies have shown that long-term and regular TC exercise can effectively improve static balance and coordination ability,^[28,29]^ increase the strength of periarticular muscle groups through resistance exercises,^[30]^ relieve joint pain,^[31]^ relieve joint stiffness,^[32]^ and promote the recovery of joint function, which is superior to non-drug surgical treatments such as hydrotherapy.^[33]^ Some scholars believe that TC can activate neuroendocrine and autonomic nervous functions, secrete neurochemicals, cause behavioral responses in analgesic pathways, and then regulate inflammatory responses of the immune system.^[34,35]^ In the process of training, the trainees always keep the posture of slightly bent knees and horse-riding step. With the changes of movement, the center of body rotates constantly, which is conducive to self-repair and stability mechanism, release endogenous neurohormones, and achieve the purpose of maintaining balance.^[36]^ At present, no serious adverse events related to TC have been reported.^[37,38]^ As a kind of KOA exercise therapy, TC is widely recognized as a kind of exercise therapy for KOA patients.

The purpose of this randomized controlled trial is to examine the effects of TC on lower extremity function and relaxation ability in patients with KOA. Since there is no standard large-sample clinical study to evaluate the effects of TC on lower extremity function and relaxation ability in patients with KOA, we intend to evaluate its efficacy in a prospective randomized controlled study.

There are also some limitations of this study: the short follow-up period does not allow us to understand the impact of long-term outcomes, so we may extend the follow-up period if necessary.
